### Participant timeline

The participant timeline is summarised in Fig. 1. The four phases of the trial will include pre-intervention surveys, 3 years of intervention, and post-intervention surveys.

### Sample size

A cross-sectional sample of 100 women in each of 48 clusters at baseline and 150 at follow-up provides more than 80% power at 5% significance level to detect a minimum difference of 6% between arms in 12-month prevalence of domestic violence, reflected in either primary outcome. This minimum difference is considered conservative because of the 3-year intervention duration. Our power estimates are based on a range of intracluster correlation coefficients (ICCs) around 0.02 assumed to apply at both baseline and follow-up, for values of cluster autocorrelation ranging from conservative (0.5) to realistic (0.8), and a range of prevalence values for the control arm at follow-up around 15% for physical or sexual violence in the preceding 12 months and 80% for emotional or economic domestic violence, control, or neglect. Values assumed for the ICC and prevalence of each outcome are derived from a preliminary analysis of baseline data, pooling data from both arms. In an analysis of 5122 records (~ 100 per cluster), mean and median cluster prevalence of physical or sexual domestic violence in the preceding 12 months was 14% (minimum 2%, maximum 29%, interquartile range 10–17%). The ICC was 0.02 (95% CI 0.01, 0.03).

### Recruitment

Forty-eight clusters of 500 households each will be mapped and potential participants identified by visiting each house. Sampling will be by systematic interval with random start. Each participant will be visited by a field data collector to discuss the process, explain the trial, and receive a participant information sheet.

### Allocation sequence generation

Allocation will be through computer-generated pseudorandomisation, in four blocks corresponding to the four phases of implementation.

### Allocation concealment mechanism

Allocation will be done using cluster numbers that mask the allocator to geographical cluster identity.

### Implementation of allocation

Allocation will be done by a senior researcher (absent the trial statistician). The numerical allocation list will be matched with cluster name and location lists by the evaluation manager.

### Masking

Trial analysts will be masked to the association between numerical allocation of clusters and the names and locations of the clusters themselves. They will also be masked to allocation arm for interim and final analyses.

### Data collection

The TARA trial addresses questions in three broad categories, based on a published theory of change [35]:
*Effects*. Did the intervention work? Were effects seen on the primary, secondary, and intermediate outcomes specified in the theory of change?*Resources and activities*. How well was the intervention done? What were the fidelity, reach, and quality of the activities?*Explanation*. How did the activities achieve—or fail to achieve—the changes specified in the theory of change?

The trial will use data from eight sources:
A cross-sectional quantitative survey with women after 3 years of community intervention delivery, including questions about physical and mental health, experience of violence, disclosure to others, and help-seekingA cross-sectional quantitative survey with women and men after 3 years of community intervention delivery, including questions about gender issues, attitudes towards violence against women and girls, bystander intervention, collective efficacy, and social capitalA cross-sectional quantitative survey with 15 women group members after 1.5 years of community intervention delivery, including questions about their understanding of violence, referral and intervention, group dynamics, and participation in group activitiesA cross-sectional quantitative survey after 1.5 years of community intervention delivery with 20 women per cluster about knowledge of, attitudes towards, and participation in groups and events, knowledge and use of services, as well as attitudes and norms around gender equalityA management information system (MIS) recording group meetings, individual and collective community actions, casework, referral, counselling and psychologist support, and campaigns and community eventsQualitative research in intervention clusters, i.e. a series of purposively sampled case studies using ethnographic and qualitative methods such as participant observation, in-depth interviews, and focus group discussions with participants and groups, designed to contribute to the formulation of theory about intervention context, mechanisms, and outcomes [36–38]A battery of assessments of the quality of mobilisation, facilitation, group processes, and supervision, collected annually for 3 yearsA cohort of survivors of violence, with or without associated mental health concerns, recruited at the point of service consultation and followed up with individual interviews.

### Data management

Data will be entered at source into an electronic database, using Android tablets running Dimagi CommCare (https://www.dimagi.com/commcare/). The front end will incorporate display conditions and field constraints to optimise quality. Field supervisors will observe 5% of interviews, 10% of uploaded forms will be checked, and online databases will be downloaded daily for back-up. Data will be collected and stored by SNEHA, under an agreement with University College London (UCL), and in accordance with the UK Data Protection Act 1998 and the General Data Protection Regulation 2018.

### Statistical methods for primary and secondary outcomes

We will present a trial profile and comparisons of allocation group characteristics and trial indicators at baseline and follow-up. Proportions of primary and secondary outcomes will be reported by allocation group. Primary intention-to-treat analysis of intervention effect will be based on baseline and post-intervention data combined, using logistic regression with random effects for clusters. No formal adjustment to the standard 5% significance level will be made on the basis of two primary outcomes. We expect a residential turnover of ~ 25% per annum, addressed in ancillary ‘per protocol’ analyses of subgroups resident over the trial period. An analysis plan will be developed, examined by the Trial Steering Committee (TSC), and sealed prior to completion of data collection.

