### Setting

We will select 48 informal settlement (slum) clusters, each of 500 dwellings, in Mumbai after vulnerability assessment. We will allocate 24 clusters randomly to receive the intervention and 24 to control. The trial will be implemented in four phases, each including six intervention and six control clusters. Each phase will begin with a pre-intervention survey. The intervention will be implemented for 3 years in each phase, followed by a post-intervention survey (see Fig. 1).

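### The primary model for the pooled surveys names no cluster-by-period effect although power assumes a cluster autocorrelation of 0.5 to 0.8; fitted with one random intercept per cluster, the 5% test would run at roughly 10% to 20%

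*Protocol article*

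**What the plan says.** The Statistical methods section gives the primary model in one sentence: "Primary intention-to-treat analysis of intervention effect will be based on baseline and post-intervention data combined, using logistic regression with random effects for clusters". It does not say whether the random effects include a term that varies between surveys, or how the baseline data enter (arm-by-period interaction, or arms set equal at baseline). It adds that an analysis plan will be written later and sealed before data collection ends.

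The Sample size section describes the design as "A cross-sectional sample of 100 women in each of 48 clusters at baseline and 150 at follow-up". It claims "more than 80% power at 5% significance level to detect a minimum difference of 6% between arms", using "a range of intracluster correlation coefficients (ICCs) around 0.02 assumed to apply at both baseline and follow-up" and doing so "for values of cluster autocorrelation ranging from conservative (0.5) to realistic (0.8"). The ICC estimated from baseline data for physical or sexual violence is 0.02, with a 95% confidence interval of 0.01 to 0.03.

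**The concern.** The two surveys are separate cross-sections, so the cluster is the only link between them. A single random intercept per cluster treats a cluster's underlying prevalence as identical 3 years apart, except for the fixed period and treatment effects. That is an autocorrelation of 1, above even the value the protocol calls realistic. The protocol also expects residential turnover of about 25% a year; if that were constant and independent, about 0.75³ = 42% of residents would remain after 3 years, so drift is plausible.

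If clusters drift and the model has no term for it, the drift enters the estimated effect but not its standard error. Intervals would be too narrow and p values too small for both primary outcomes, each tested at 5% without adjustment. The trial could then report a reduction or an increase in violence at two or more times the stated error rate.

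**Working it through.** **Inputs.** 24 clusters per arm (Setting). From Sample size: 100 women per cluster at baseline and 150 at follow-up; ICC ρ = 0.02, with 0.01 and 0.03 from its confidence interval; cluster autocorrelation (CAC) 0.5 and 0.8; control prevalence 15% and 80%; difference 6 points; 5% significance. Sidedness is not stated, so two-sided is assumed. Variances are in units of p(1−p).

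**1. The plan's own power figure.**
- Baseline cluster mean: v0 = 0.02 + 0.98/100 = 0.0298.
- Follow-up cluster mean: v1 = 0.02 + 0.98/150 = 0.02653.
- Covariance: c = 0.02 × CAC = 0.010 or 0.016.
- Baseline-adjusted variance, v1 − c²/v0: 0.02318 (CAC 0.5) or 0.01794 (CAC 0.8).

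For 80% versus 74%, SE = √[(0.80×0.20 + 0.74×0.26) × variance / 24], which is 0.01845 or 0.01623. Power = Φ(0.06/SE − 1.96) = 90.2% or 95.9%. For 15% versus 9% it is 98.8% or 99.8%. Over ICC 0.01 to 0.03 the lowest value is 80.5% (80% versus 74%, ICC 0.03, CAC 0.5). The claim of more than 80% is reproduced, using a variance structure with CAC below 1 and baseline adjustment.

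With an unconstrained arm-by-period contrast the variance is v0 + v1 − 2c = 0.03633 at CAC 0.5. Power for 80% versus 74% is then 73.8%, and the claim is not reproduced.

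**2. What a single intercept would report.** Per-cluster variance of the change between surveys:
- Single-intercept model: 0.98 × (1/100 + 1/150) = 0.0163.
- With drift, add 2 × 0.02 × (1 − CAC): 0.0363 (CAC 0.5) or 0.0243 (CAC 0.8).
- Variance ratios 2.22 and 1.49; SE factors 1.49 and 1.22.
- Actual error, 2[1 − Φ(1.96/SE factor)]: 18.9% and 10.8%.

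Allowing the fitted variance components of a linear mixed model to absorb what they can changes little. The error is 18.8% and 10.8% for the arm-by-period form. It is 16.8% and 10.0% with arms constrained equal at baseline (variance ratios 2.02 and 1.42).

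**3. Simulation of the logistic model.** One random intercept per cluster, Wald test, ICC 0.02, 1,500 trials per setting. Each cell gives the rejection rate under no effect at prevalence 15% / 80%.

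| CAC | Arm-by-period | Arms equal at baseline |
|---|---|---|
| 0.5 | 20.0% / 20.5% | 18.3% / 16.5% |
| 0.8 | 11.1% / 10.6% | 10.2% / 10.8% |
| 1.0 | 4.8% / 5.7% | 4.9% / 5.7% |

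A separate set of 1,000 trials per setting gave somewhat lower rates at CAC 0.5 (17-18% and 15-16%) and about 11% at CAC 0.8. The rate is close to 5% at CAC 1, so the inflation comes from the omitted cluster-by-period variation.

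**4. Range over the ICC interval.** By formula, the error runs from 7.2% (ICC 0.01, CAC 0.8, arms equal at baseline) to 24.4% (ICC 0.03, CAC 0.5, arm-by-period).

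**5. Analyses that allow drift.** Cluster-level analyses on empirical logits (5,000 trials per setting, ICC 0.02) gave type I error of 4.6% to 5.4%. Power for 80% versus 74% at CAC 0.5 and 0.8 was 84.5% and 92.1% with baseline adjustment, against 67.3% and 82.8% for change scores.

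**The case against.** The strongest reply is that the protocol does not say what the calculation presumes. It speaks of random effects, in the plural, for clusters; it says neither a single random intercept nor cluster effects alone. A cluster-by-period effect is itself a random effect at cluster level. The Sample size section shows that the authors had the right variance structure in mind. A condensed article may leave the full random-effects specification to the analysis plan, which is announced but not shown.

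Much of this stands. A reader might infer that the model has only a cluster intercept and that the primary tests really do run at 11% to 18%. The text supports neither: the first is one reading of an open phrase, and the second also needs model-based standard errors and particular values of ICC and autocorrelation. The autocorrelations are planning values that baseline data alone cannot estimate, and the protocol labels 0.5 as conservative, so about 11% is the figure at its realistic value. The ICC interval is reported only for physical or sexual violence; the other outcome has only a planning value around 0.02. Nor should a reader infer that the power statement is wrong, since it reproduces with baseline adjustment.

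What does not stand is that nothing needs saying. The protocol did choose a primary model, the usual reading of its sentence is one intercept per cluster, and an analyst who followed that reading would run an anti-conservative test under the protocol's own assumptions.

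**Conclusion.** The concern holds in conditional form. The primary analysis sentence does not carry the cluster autocorrelation below 1 on which the sample size rests. If it is fitted as ordinarily read, with model-based standard errors, the nominal 5% test runs at about 10-11% at autocorrelation 0.8 and 17-20% at 0.5, for ICC 0.02. Over ICC 0.01 to 0.03 the range is about 7% to 24%, above 5% throughout. The conclusion assumes a two-sided test and the protocol's planning autocorrelations. It would fall away if the analysis plan already specifies a cluster-by-period effect or an equivalent.

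**What to change.** In the Statistical methods section and in the analysis plan, specify a logistic mixed model with a cluster random effect and a cluster-by-period random effect, with the arms constrained equal at baseline. An equivalent is an analysis of follow-up data adjusted for the cluster's baseline prevalence. Either should use small-sample inference suited to 48 clusters.

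The change takes a sentence or two. The price is honest standard errors: on the change-between-arms form they are about 22-49% larger than the single-intercept model would report. With the baseline constrained, that model understates its own standard error by a little less (√1.42 = 1.19 to √2.02 = 1.42).

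The handling of baseline must be part of the same sentence. With adjustment or constraint, power for 80% versus 74% at ICC 0.02 stays above 80%. An unconstrained arm-by-period model with the added random effect would correct the error rate but, at autocorrelation 0.5, lose the stated power.

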### Additional analyses

#### Effects: did the intervention work? Were effects seen on the primary, secondary, and intermediate outcomes specified in the theory of change?

Based on the programme theory of change, Additional file 1: Table S1 summarises the indicators we will use to evaluate effects and how we will collect them.

#### Resources and activities: how well was the intervention done? What were the fidelity, reach, and quality of the activities?

Based on the programme theory of change, Additional file 2: Table S2 summarises the indicators we will use to evaluate delivery, fidelity, quality, and the range and degree of responses to the community mobilisation intervention, and how we will collect them.

#### Explanation: how did the activities achieve—or fail to achieve—the changes specified in the theory of change?

##### Year 1: understanding context

A context document will describe the circumstances in which and people with whom intervention activities take place. Sources of information are summarised in Additional file 3: Table S3.

##### Year 2: developing hypotheses about what worked, for whom, and in what circumstances

Taking account of the contextual constructs identified in Year 1 (Additional file 2: Table S2), we will take a realist approach to developing hypothetical context-mechanism-outcome (CMO) configurations [39]. The means by which we test these configurations will be method-neutral, combining quantitative intervention monitoring data with qualitative data from interviews and observation of community activities.

##### Year 3: testing and refining hypotheses

We will test the candidate CMO configurations developed in Year 2 using a combination of quantitative and qualitative data. Beginning in Year 1, we will have developed longitudinal case studies in groups and neighbourhoods, and we will combine these with quantitative information on group attendance, activities, and outcomes.

#### Data monitoring

The trial will be governed by a combined independent TSC and a Data Monitoring and Ethics Committee (DMEC), and a SNEHA-UCL Trial Management Group (TMG), following Medical Research Council (MRC) and DAta Monitoring Committees: Lessons, Ethics, Statistics (DAMOCLES) terms of reference [40, 41]. The TSC will meet annually to provide oversight [42, 43]. The first meeting will take place after ethical approval and before recruitment begins, to review the protocol and establish the DMEC. Subsequent meetings will be annual. Information provision and TSC reporting templates will be used [43]. The DMEC will also meet annually [40]. We will undertake interim analyses for the DMEC. No stopping rule is envisaged. Charters for committees can be provided on request to the principal investigators.

#### Harms

The backbone of the trial is the provision of an extensive range of support services for survivors of violence. All investigators and intervention team members will be trained to respond to adverse events according to existing organisational protocols. Community organisers, supervisors, and interviewers will follow these protocols for response to survivors of domestic violence, non-partner sexual violence, or child sexual abuse. The protocols include immediate response (active listening, safety assessment, assessment of suicidal ideation, validation and support, psychological first aid, consideration of shelter, admission to hospital if necessary), enlisting of immediate help from line managers, doctors, or the police if required, and then provision of information and referral to an in-house counsellor. Subsequent arrangements encompass legal support, psychologist assessment and mental health counselling, and follow-up. The response to intervention activities may also follow ‘dark logic’ [44], elaborated in the theory of change. A woman’s disclosure of violence may lead to reprisals and a short-term increase in abuse, our activities may trigger vigilantism and precipitate action, people may demand that we support the perpetrator rather than the survivor, the wrong person may be punished, perpetrators may change the type of abuse they are enacting, or (ostensibly protective) limits may be set to women’s mobility. There is a small but important possibility of threats to team members and family or community hostility. We have substantial experience in dealing with each of these eventualities, including protocols for response to threat, in-house lawyers, and strong connections with the police.

#### Ancillary and post-trial care

Any participant or non-participant in trial areas will have free and open access to the full range of SNEHA support services.

## Discussion

A recent set of systematic reviews of interventions to prevent violence against women and girls developed a typology of effectiveness and the quality of evidence for it. Community mobilisation was rated as a promising population-based intervention [45], and included participatory projects and community-driven development engaging multiple stakeholders and addressing gender norms. Group-based training or workshops for prevention of violence against women and girls included empowerment training (rated as promising), work with men and boys on norms (rated as conflicting), and community workshops to promote changes in norms and behaviour (rated as promising) [23].

We lack adequately powered trials of clearly defined interventions of sufficient duration to have meaningful effects. We have identified 13 randomised trials of interventions to reduce domestic violence against women and girls in low- and middle-income countries. Six had urban components [46–51], 11 were in Africa [46–50, 52–57], and one in South Asia [51]. Seven of the trials combined violence prevention activities with HIV prevention [46–48, 50, 52, 56, 58], and four with enterprise and microfinance [52, 53, 55, 58]. In South Africa, the Intervention with Microfinance for AIDS and Gender Equity (IMAGE) study added to microfinance Sisters for Life, a 10-session programme followed by community mobilisation to engage adolescents and adult males. In a sample of 538 from eight clusters, reported past-year intimate partner violence was halved (adjusted risk ratio 0.45; 0.23, 0.91) [58]. In Uganda, the Safe Homes and Respect for Everyone (SHARE) study added community mobilisation to HIV prevention activities. The intervention involved efforts to change attitudes, social norms, and behaviours related to intimate partner violence. After 3 years, in a sample of 7842 in four intervention and seven control clusters, reported past-year physical (adjusted prevalence rate ratio 0.79; 95% CI 0.67, 0.92) and sexual (0.80; 0.67, 0.7) intimate partner violence were reduced [50]. Also in Uganda, the SASA! intervention recruited community activists to encourage change in norms, attitudes, and behaviours. After about 3 years, in a sample of 2532 in eight clusters, reported past-year physical (odds ratio 0.48; 0.16, 1.39) and sexual (0.76; 0.33, 1.72) intimate partner violence were substantially, but non-significantly, reduced [48, 59]. A couples intervention in Rwanda reduced physical and sexual intimate partner violence in the preceding 12 months [57], and a combination of community mobilisation, group work, and service provision has been trialled in urban Bangladesh [51].

We aim to address known deficiencies in evaluation and partnership. Research on violence against women and girls has been limited, given its ubiquity and health burden, and has favoured description of prevalence and risk factors [5]. Interventional evaluations have tended to focus on high-income countries and on response rather than prevention [23]. Evaluation of the effects of programmes is a priority, particularly through theory-informed testing of interventions to address gender inequality and social norms that legitimise violence [24, 26]. Competent evaluation remains a challenge, non-governmental organisations (NGOs) need to improve their evaluative capacity, and researchers need to partner with implementors [11, 12]. Backed by public engagement, advocacy, and open publication, our vision is of a replicable community-led intervention to address the public health burden of violence against women and girls.

### Ethical considerations

The trial involves data collected on a sensitive subject from women, some of whom will be survivors of violence, in order to evaluate a community intervention that discusses and acts to prevent violence against women. There are three general areas of ethical interest: data collection, intervention, and trial design.

Interviewing women about their possible experience of violence, and men about their views on it, raises issues of consent, interviewer behaviour, privacy and confidentiality, and data sharing. Particular issues we have identified include duty of care after disclosure, breach of confidentiality, veiling of interview content, and perpetration. Duty of care is an issue that we have debated at length, particularly since we do not see a substantial treatment of it in previous research and trials. We feel strongly that an interviewee who discloses experience of violence—physical, sexual, emotional, or gender-based household maltreatment—should be offered optimal support. This goes well beyond presenting her with a list of contact details for local services. Interviewers will be members of a team that is able to provide a full suite of crisis and counselling services, including home visits, medical, surgical, and psychiatric referral, and negotiation with families, the police, and legal representatives.

Although we have not experienced resistance to our community activities in the past 17 years, we assume that the subject of violence against women and girls is not one that communities might readily identify as a problem. Gatekeeper consent is an issue under discussion in cluster trials. The most authoritative review suggests that it is not mandatory [60, 61]. Particular issues are the right of individuals to speak for clusters when the clusters themselves are informal [62], that prominent individuals may not have authority to decide on health issues [63], and that gatekeeper permission implies acceptance of the structural arrangements that underlie gender inequity. Nevertheless, because it is good practice for community interventions, we will seek formal permission from gatekeepers identified by cluster residents. In the same way as for data collectors, we will ensure that community intervention team members are trained and supervised in the ethics of work on violence against women. This extends to confidentiality: group activities are part of the intervention, and facilitators must make it clear to participants that individuals need to be protected.

As with other trials of complex public health interventions, we are testing an intervention that, if successful, will be extended subsequently to control areas. The idea of equipoise will be explained in meetings with cluster gatekeepers. A key issue is benefits to control areas. Our trial differs from other trials, we think, in an important way. Previous trials have tested the effectiveness of community mobilisation and awareness, but have not been grounded in an extensive service network. Our hypothesis is that community mobilisation will offer more benefit than support services alone. We will therefore extend our existing services to cover all clusters, control and intervention. This is similar to the way in which our programme currently supports women and girls who live outside our community action areas. We will make sure that women and girls in these areas have access to all the support agreed by the Council of Europe Istanbul convention [64]. Key compliances achievable at the non-governmental level are condemnation of discrimination against women, prevention through attitudinal and norm change, helping survivors get support through hotlines, shelter, medical, psychological, and legal counselling, protecting women at risk through emergency orders, risk assessment and management, providing support and protection to survivors in judicial proceedings, and collecting epidemiologic and evaluative data.

